## Materials and methods

### Patient and public involvement, trial design

Before launching the trial, a few pre-implementation studies were conducted together with the partner community organisations across three provinces (British Columbia, Manitoba, Saskatchewan) and adult participants aged 55 + . We completed one virtual focus group per province with staff from each of the partner sites to gather input on how to adapt The CONNECT Program for different provinces [41–43]. This included feedback on revising the materials to reflect local needs, choosing the best delivery format (phone or videoconferencing), and designing a training and supervision process for community-based facilitators. We also held virtual focus groups and interviews with adults aged 55+ to learn about their mental health support needs, views on The CONNECT Program and implementation preferences [44].

This study uses a randomized crossover trial design, embedded within a type 1 hybrid implementation-effectiveness framework [45]. Participants are randomly assigned in a 1:1 ratio to begin either with The CONNECT Program or with the community-based programming. After completing the first condition, they will cross over to the other condition. Two sites will begin with videoconference mode and then switch to telephone mode, while the other two will follow the opposite sequence. In this RCT the effectiveness and implementation outcomes follow a superiority framework. Recruitment is ongoing in four Canadian provinces, with site-specific recruitment periods. The recruitment started on 8 September 2025, and is ongoing, with recruitment date for both primary and secondary end point collection expected to be collected by 30 September 2026.

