Risks of the trial are minimal but may include psychological and emotional discomfort when discussing topics like social isolation, loneliness or mental health. Facilitators monitor participants during sessions and respond to distress following a structured safety protocol. A mental health resource list is provided to all participants, and those in the control condition continue to receive service as usual.

The trial has a target recruitment of 128 participants, with 64 in each delivery group (videoconference and telephone), based on a power calculation with Cohen effect of 0.5 alpha = 0.05 and power 80%. The effect size of 0.5 is based on our pilot data and is consistent with other similar intervention studies in older adults (e.g., [66]).

Participants will be recruited through the four partnering community organizations, with local community partners overseeing outreach. Each site will run two groups per delivery mode (videoconference and phone), with approximately 32 participants recruited per site. To support both recruitment and retention, participants will receive a $25 honorarium (e-gift card or mailed) after completing each of the three assessment points baseline, post-intervention, and follow-up – for a total of $75. An additional $25 honorarium will be provided to participants who are selected at random for qualitative interviews after participating in The CONNECT Program (n = 40; 10 per site).

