Analysis of the primary and secondary outcomes will be conducted using linear mixed-effects models to account for repeated measures and the crossover design. Changes in psychological flexibility, loneliness, social isolation, emotional support, anxiety, depression, and mental health literacy will be compared between The CONNECT Program and control conditions using repeated measures analyses, adjusting for delivery sequence and baseline values. For descriptive comparisons, both paired t-tests and repeated measures ANOVA may be used. Adverse events and participant distress will be recorded; however, harms will not be systematically evaluated. All analyses will be performed on a per-protocol basis, including only participants who complete both stages. Sensitivity analyses may include a larger sample, if applicable. Missing data will be examined for patterns; if data are missing at random, linear mixed models will be used. For key outcomes with high levels of missingness, multiple imputation or pattern-mixture models will be considered. Subgroup analyses by delivery mode and location will be conducted if sample sizes are sufficient to support interpretation.

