## Discussion

The CONNECT Program is a unique mental health support program aimed at addressing the critical service gaps faced by older adults who are experiencing social isolation, loneliness, and mental health difficulties. While our primary aim with this trial is to assess program impact on key mental health outcomes, a secondary aim is to provide real-world evidence about its implementation in different community-service settings. Also, there are a number of design and other administrative issues that should be considered. Although the hybrid trial design allows for simultaneous assessment of implementation and effectiveness outcomes, it may also complicate data interpretation. Contexts between distinct sites vary, potentially confounding attribution of outcomes to intervention.

The individual-level crossover design increases internal validity but may be affected by carryover effects between treatment periods, even with the relatively short 6-week program and no formal washout. Psychological changes may persist and influence subsequent measurements.

Furthermore, tablets and technical support will be offered, and the technological literacy of adults 55 + might influence their engagement, particularly when it comes to the delivery videoconferencing delivery. This can also affect both the implementation and effectiveness data.

Findings from this study will yield critical insights regarding the effectiveness and implementation of The CONNECT Program in a variety of community settings and delivery modalities. Given the urgent need for accessible interventions for socially isolated older adults, a successful outcome of this trial could pave the way for The CONNECT Program to be disseminated broadly as a tool to combat the epidemic of loneliness and mental health challenges in the aging population.

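### Table 1 gives the CONNECT-first arm no week-12 assessment, so the crossover model as worded may estimate a one-arm before-after change instead of the randomised week-6 difference

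*Protocol article*

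**What the plan says.** The trial design section describes a two-sequence crossover: "Participants are randomly assigned in a 1:1 ratio to begin either with The CONNECT Program or with the community-based programming", with a switch between weeks 6 and 7. The statistical analysis paragraph (under Assignment of interventions) plans "linear mixed-effects models to account for repeated measures and the crossover design" and says that outcomes "will be compared between The CONNECT Program and control conditions using repeated measures analyses, adjusting for delivery sequence and baseline values". It restricts all analyses to participants who complete both stages.

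Table 1 marks AAQ-II and the six secondary scales at week 0, week 6 and T5 for both sequences. At week 12 it marks them only for participants who receive CONNECT second. The note to Fig 1 sets T5 at 24 weeks after each participant finishes CONNECT. The honorarium text counts three assessment points, which fits a CONNECT-first arm with no week-12 visit.

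The sample size of 128 is "based on a power calculation with Cohen effect of 0.5 alpha = 0.05 and power 80" per cent. The Discussion accepts that the design "may be affected by carryover effects between treatment periods, even with the relatively short 6-week program and no formal washout".

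**The concern.** A crossover analysis needs each sequence measured at the end of both periods. Here one of the four sequence-by-period cells is not scheduled. T5 cannot fill it, because it is timed from the end of CONNECT in both arms and is not an end-of-control measurement.

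With that cell empty, CONNECT-first contributes only CONNECT observations after baseline, so a term for treatment order can absorb the whole arm. What remains is a before-after change in the other arm. Participants enrol because they report loneliness, isolation or mental health challenges, so natural change over 12 weeks is plausible. The randomised comparison at week 6 is available and free of this problem, but nothing in the wording makes it the primary contrast.

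**Working it through.** **The plan's own figure.** For two independent groups, d = 0.5, two-sided alpha 0.05 (sidedness assumed) and power 80%, the t-test needs 63.8, so 64 per group and 128 in total, with power 80.1%. A paired test with standardised difference 0.5 would need 34 in total. The stated 128 is thus a parallel-group calculation. The article describes the two groups of 64 as delivery modes, but 1:1 allocation of 128 also gives about 64 per sequence.

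**Scheduled post-baseline cells, excluding T5.**

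| Sequence | Week 6 | Week 12 |
|---|---|---|
| CONNECT-first | CONNECT | not measured |
| Control-first | control | CONNECT |

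**What each model estimates.** Weights are on (CONNECT-first week 6, control-first week 6, control-first week 12).

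- Condition + treatment sequence: 3 parameters on 3 cells, so the fit is exact. The condition weights are (0, -1, +1). A mixed model fitted to one simulated dataset gave 0.2497, and the paired week-12 minus week-6 mean was also 0.2497.
- Condition + period: weights (+1, -1, 0). This is the week-6 contrast, and week 12 adds no treatment information.
- Condition + sequence + period: 4 parameters, rank 3. Condition is not identified.

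**Size of the problem under no true effect.** Assumptions: 64 per sequence, common correlation r between visits, common drift from week 6 to week 12, 2,000 simulated trials per scenario. The document gives neither drift nor correlation. Rejection rates at nominal 5%:

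| Drift (SD) | Condition + sequence, r = 0.5 / 0.7 | Condition, no sequence term, r = 0.5 / 0.7 |
|---|---|---|
| 0 | 4% / 5% | 5% / 5% |
| 0.1 | 13% / 16% | 9% / 12% |
| 0.2 | 36% / 54% | 22% / 34% |
| 0.3 | 67% / 87% | 44% / 65% |

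All models also included baseline. The week-6 contrast stayed at about 4% to 6% throughout. With the sequence term the bias is the full drift. Without it, about two thirds of the drift enters (0.134 to 0.138 for a drift of 0.2).

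Closed-form check at r = 0.6: the SE of the paired change is sqrt(2 × 0.4 / 64) = 0.112 SD. Drifts of 0.15 and 0.30 SD give z = 1.34 and 2.68, or about 27% and 76% rejection.

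**If the outcome is change within each period.** The condition + sequence contrast becomes (week 12 - week 6) - (week 6 - week 0) in the control-first arm. Constant drift cancels. An assumed change of -0.3 SD and then -0.1 SD gives -0.1 - (-0.3) = +0.20 SD, which counts against CONNECT because lower AAQ-II is better. The contrast is still one-arm and non-randomised.

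**Power of the week-6 contrast.** Power = Φ(0.5 / [sqrt(1 - r²) × sqrt(2/64)] - 1.96), where r is now the baseline correlation. For r = 0, 0.3, 0.5 and 0.7 this gives 81%, 84%, 90% and 98%, before attrition and group clustering.

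**The case against.** The strongest reply is that the article gives no model formula. A phrase about adjustment in a condensed protocol need not list every fixed effect, and a period or visit factor may sit in an analysis plan that is not shown. That stands: a missing period term alone is no finding. But adding period beside treatment sequence leaves the effect unidentified on this schedule, and replacing sequence with period reduces the model to the week-6 contrast. The printed schedule and the wording conflict either way.

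Second, delivery elsewhere in the article usually means telephone or videoconference, and sites run the modes in opposite orders. Under that reading the week-6 contrast does contribute, so a reader who infers that the planned effect is certainly a before-after change goes too far. The time bias is then diluted to about two thirds, not removed.

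Third, the paragraph speaks of changes. If these are within-period, drift need not favour CONNECT, so it is not established that the model would always credit drift to the programme.

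A reader might also infer that carryover biases the planned result, since the Discussion says "Psychological changes may persist and influence subsequent measurements" and there is no washout. The schedule does not support that: the period in which carryover from CONNECT would show is never measured at its end. Only if week 12 were added for CONNECT-first would it matter. A full crossover with a period term averages the two period contrasts, so a true effect of -0.50 SD would become (-0.50 + 0)/2 = -0.25 with full carryover and (-0.50 - 0.25)/2 = -0.375 with half.

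**Conclusion.** The point holds in a conditional form. That CONNECT-first has no end-of-control measurement is plain from Table 1. The zero weight on the randomised contrast is exact algebra if delivery sequence means treatment order and post-baseline levels are analysed without a period term. The 13% to 87% range rests on assumed drift and correlation; with no drift, the error rate is nominal. Under the mode-order reading the bias is smaller, and under the within-period reading its direction depends on the time course. No reading yields a pooled crossover effect that is both identified and free of confounding with time. Recruitment is ongoing, so this can be settled before analysis.

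**What to change.** - State the primary effect as the CONNECT-first minus control-first difference in AAQ-II at week 6, adjusted for baseline, by ANCOVA or by a mixed model with arm-by-visit terms and the week-6 contrast.
- Analyse all randomised participants with week-6 data. Restricting to completers of both stages selects on events after randomisation and would weaken this comparison too.
- Report week 12 and T5 descriptively, and keep second-period data out of the primary effect.
- Reconcile Table 1 with the crossover wording, and say what delivery sequence and changes mean. If week 12 is to be measured in both sequences, include period and justify assuming no carryover.

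The main changes are wording only and need no new data or participants. The cost is the nominal within-person efficiency of a crossover, which this schedule does not deliver. Adding the week-12 assessment in CONNECT-first would be extra data collection and is not needed for the primary effect.

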### Acceptability of The CONNECT program

Acceptability is defined as the perception among implementation stakeholders that a given treatment, service, practice, or innovation is agreeable, palatable, or satisfactory [63]. Data will be collected through a post-program survey that includes Likert-scale and open-ended questions (with items developed based on [63]), an exit interview, the Intervention Content evaluation (adapted from [64]), and the Intervention Delivery Type evaluation (also adapted from [64]), and the Group Session Rating Scale [65], administered weekly during The CONNECT Program. In addition, a weekly facilitator check-in questionnaire will track dropout, attendance, and participant-reported reasons for not attending or discontinuing.

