### Sustainability of The CONNECT program

Sustainability is defined as the extent to which a newly implemented treatment is maintained or institutionalized within a service setting’s ongoing, stable operations [63]. Data will be collected through a post-program survey that includes Likert-scale and open-ended questions (with items developed based on [63]). In addition, a weekly facilitator check-in questionnaire will track dropout, attendance, and participant-reported reasons for not attending or discontinuing.

A detailed overview of the assessment schedule by timepoint and study week is provided in Table 1.

**Table 1 pone.0336031.t001:** Schedule for assessment administration.

	TRIAL PERIOD						
	Enrollment		Post-randomization				6-month follow-up
Timepoint	*−1*	0	*T1*	*T2*	*T3*	*T4*	*T5*
Timing	*Week *(−4)	Week 0	*Week 1 -Week 6*	*Week 6*	*Week 7 -Week 12*	*Week 12*	*Week 30–36*
Sociodemographics		X^1,2^					
Psychological flexibility (Acceptance and Action Scale; [47]) Acceptance and Commitment Scale		X^1,2^		X^1,2^		X^2^	X^1,2^
DeJong Gierveld Loneliness Scale [53]		X^1,2^		X^1,2^		X^2^	X^1,2^
Social Isolation (PROMIS Social Isolation 8a; [55]		X^1,2^		X^1,2^		X^2^	X^1,2^
Emotional Support (PROMIS Emotional Support; [55])		X^1,2^		X^1,2^		X^2^	X^1,2^
Anxiety (PROMIS Anxiety Short Form 4a; [56])		X^1,2^		X^1,2^		X^2^	X^1,2^
Depression (PROMIS Depression Short Form 4a; [56])		X^1,2^		X^1,2^		X^2^	X^1,2^
Mental Health Literacy (Brief Mental Health Literacy Scale; [61]		X^1,2^		X^1,2^		X^2^	X^1,2^
Group Session Scale [65]			X³		X³		
Intervention Delivery Type (Adapted from [64]				X^1^		X^2^	
Intervention Content (Adapted from [64]				X^1^		X^2^	
Individual Qualitative Exit-Interview				X^1^		X^2^	
Implementation Survey (Likert-scale and open-ended items, per [63].)				X^1^		X^2^	
Weekly Facilitator Check-in Questionnaire			X³		X³		

X¹ - Participants who received The CONNECT Program first, X² - Participants who received The CONNECT Program second (after waitlist), X³ - Weekly administration during the CONNECT Program sessions only; not completed during control condition.

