### Monitoring

A formal Data Monitoring Committee (DMC) was not impaneled for this trial because The CONNECT Program is a low-risk, non-pharmacological behavioral intervention. In accordance with ethical conduct, the principal investigator and study team will provide monitoring of this study. Interim analyses or stopping guidelines are not planned with this short trial and small number of enrolled participants, who are exposed to little risk. Any negative experiences or unexpected issues (e.g., distress among participants) will be managed by the study team. The study coordinator and principal investigator will oversee the daily administration of the program – recruitment, delivery of interventions, attendance, and data collection. The study team will meet on a regular basis to review the progress of the trial and consider any new issues, which have arisen.

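### Adverse events and distress are recorded but not systematically evaluated, and the completers-only rule removes people who leave in distress, so no balanced harms summary by condition is planned

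*Protocol article*

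**What the plan says.** The analysis paragraph of the protocol article, at the end of the section Assignment of interventions, states: "Adverse events and participant distress will be recorded; however, harms will not be systematically evaluated". The same paragraph puts all analyses on a per-protocol basis, restricted to participants who complete both stages. It adds only that sensitivity analyses may use a larger sample.

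Harm is treated as foreseeable elsewhere. The risk paragraph after Table 1 says: "Risks of the trial are minimal but may include psychological and emotional discomfort when discussing topics like social isolation, loneliness or mental health". It continues: "Facilitators monitor participants during sessions and respond to distress following a structured safety protocol". The section Participants, interventions, and outcomes describes a safety protocol for significant distress or suicidal thoughts, which may pause a participant's involvement. Under Monitoring, "A formal Data Monitoring Committee (DMC) was not impaneled for this trial" because the program is considered low-risk, and "Any negative experiences or unexpected issues (e.g., distress among participants) will be managed by the study team".

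On weekly data collection, the Acceptability section says that "a weekly facilitator check-in questionnaire will track dropout, attendance, and participant-reported reasons for not attending or discontinuing". The Table 1 footnote for that questionnaire and for the Group Session Scale reads: "Weekly administration during the CONNECT Program sessions only; not completed during control condition". Table 1 schedules the PROMIS anxiety and depression scales at week 0 and week 6 in both sequences. At week 12 they are scheduled only for those who receive CONNECT second.

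**The concern.** This is a stated rule, not a detail left to a fuller document. The data are to be collected, and what the article declines is their evaluation. An analysis plan that evaluated harms systematically would contradict the article.

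The completers-only rule compounds this. Symptom scores could partly stand in for a harms analysis, because both scales are measured in both randomised sequences at week 6. But a participant who leaves because of distress has not completed both stages and is excluded from that comparison. So is a CONNECT-first participant who gives full week 0 and week 6 data and then leaves during weeks 7-12. The people most informative about harm are the likeliest to be missing.

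Two statements in the article would then rest on little. One is the low-risk description that justifies having no monitoring committee. The other is the Discussion's expectation that a successful trial could lead to broad dissemination. An average benefit can coexist with a minority who get worse, and the plan as written commits to no summary that would show it.

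**Working it through.** **1. The design figure.** The article gives 128 participants (64 per delivery group) for d = 0.5, alpha 0.05 and power 80%. By the normal approximation, n = 2(1.96 + 0.8416)² / 0.5² = 62.8, so 63 per group. The two-sample t-test gives 63.77, so 64 per group and 128 in total, with power 0.801. The figure reproduces with a two-sided alpha. Randomisation is 1:1 to sequence, so 128 / 2 = 64 per sequence is used below. Nothing in this point changes that number.

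**2. What each source supplies on harms.**

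| Source | CONNECT period | Control period | Planned use for harms |
|---|---|---|---|
| Adverse events and distress | Recorded; method not stated | Recorded; method not stated | Not systematically evaluated |
| Weekly facilitator check-in (dropout, attendance, reasons) | Yes | No | Implementation measure |
| PROMIS anxiety and depression, weeks 0 and 6 | Yes (CONNECT-first) | Yes (control-first) | Compared between conditions, completers of both stages only |
| PROMIS anxiety and depression, week 12 | Yes (control-first) | No (CONNECT-first) | No concurrent comparison between sequences |

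The only balanced randomised comparison is weeks 0 to 6, and the completers-only rule narrows it. After week 6 there is no balanced symptom assessment, because CONNECT-first participants have no T4 visit.

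**3. What counts of this size could show.** The event rates below are assumptions; the article gives none.

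- *Upper limit with zero events*, one-sided 95%, 1 − 0.05^(1/n). For n = 64: 1 − 0.05^(1/64) = 4.6%. For n = 128: 1 − 0.05^(1/128) = 2.3%. The first fits one sequence in weeks 1-6. The second fits harm during CONNECT if all 128 receive it, as the crossover schedules.
- *Chance of at least one event during CONNECT*, 1 − (1 − p)^128. At p = 1%: 72%. At p = 2%: 92%.
- *Power to compare sequences in weeks 1-6*, two-sided alpha 0.05, 64 per sequence: Φ{[|p₂ − p₁|√64 − 1.96√(2p̄(1 − p̄))] / √(p₁(1 − p₁) + p₂(1 − p₂))}. For 5% versus 10%: [0.05 × 8 − 1.96 × 0.3725] / 0.3708 = −0.89, giving 19%. The same formula gives 47% for 5% versus 15% and 73% for 5% versus 20%.

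Recorded events can therefore show that harm occurred and bound its rate. A formal comparison would detect only large differences, so a descriptive table is the right output.

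**The case against.** The best defence is that harms are not ignored. Events and distress are recorded, anxiety and depression are compared between conditions, and people who discontinue are still invited to follow-up assessments. Facilitators are trained in safety and crisis response and can use weekly supervision, and the study team monitors the trial. The program is short and behavioural, and a reason is given for having no monitoring committee. How adverse events are collected, and what counts as worsening, are commonly left to a fuller document.

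Much of this stands, and it rules out several stronger readings:

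- A reader might infer that the trial cannot say whether the program harms anyone. The article does not support that: recorded events could be listed, and symptom worsening at week 6 could be examined.
- A reader might take the CONNECT-only weekly check-in as the channel for harms. It is described as tracking attendance, dropout and reasons. Nothing says adverse events come through it, or that their recording is confined to CONNECT. Unequal ascertainment is a risk, not an established bias.
- A reader might say a control denominator is missing. The numbers randomised to each sequence supply one. What may be missing is comparable ascertainment.
- A reader might say the symptom scores are analysed only as mean change. The article names the main models and does not exclude counts of worsening.
- The absence of a monitoring committee is a reasoned choice and is not the defect here.

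The defence does not answer the two explicit rules: no systematic evaluation, and completers only. Inviting discontinuers to follow-up does not help if the analysis then leaves them out, and the larger-sample sensitivity analysis is optional.

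**Conclusion.** The point holds in this form. The article commits to recording adverse events and distress but rules out evaluating them systematically, and it restricts all analyses to participants who complete both stages. No balanced harms summary by condition is planned, and people who leave because of distress fall out of the anxiety and depression comparisons. The unequal weekly tracking of dropout matters for harms only if events are gathered through those contacts, which the article does not state.

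The size of the problem is one of reporting, not power. At 64 per sequence the trial could not resolve modest differences under any plan. It could still give a randomised tabulation for weeks 1-6 and a bound on the event rate, and the current wording commits to neither. The bounds assume full recruitment and complete ascertainment; dropout or under-reporting would weaken them.

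**What to change.** Replace the sentence on harms in the analysis paragraph with:

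> All recorded adverse events, distress-protocol activations, and withdrawals with reasons will be tabulated descriptively for everyone randomised, regardless of completion: by randomised sequence for weeks 1-6 (the main harms comparison), and by sequence and period for weeks 7-12. The number of participants whose PROMIS Anxiety or Depression score worsens from week 0 to week 6 by a threshold fixed before analysis will be reported by sequence for all randomised participants with data.

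State that this overrides the completers-only rule for harms.

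Add one identical adverse-event/distress and withdrawal-reason item at T2 for both sequences. Put the same item to people who discontinue, through the follow-up invitation the article already plans. State that ascertainment is not balanced after week 6, because CONNECT-first participants have no T4 assessment.

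The cost is one questionnaire item, one table, a wording change, and ethics review of the amendment, which the Ethics section already provides for. Recruitment began on 8 September 2025, so anyone already past T2 will lack the new item; their number should be reported by sequence. The sample size and the interventions do not change. The output remains descriptive, and the write-up should say so.

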### Assignment of interventions

Randomization will be conducted by a non-affiliated researcher at the Centre for Healthcare Innovation (CHI) using a secure computerized tool. We are using restricted randomization to keep group sizes balanced within each site. Details about blocking and sequence structure are recorded separately and will not be shared with staff involved in recruitment or group assignment prior to randomization. Each participant will be assigned a unique ID and randomized into one of two sequences: The CONNECT Program first or Community Programming as Usual first. Participants will be randomized prior to enrollment. The research coordinator will be aware of group assignment after randomization to manage scheduling and follow-up; however, outcome assessor and outcome analysts will remain blinded and only work with de-identified data. Group assignment will not be disclosed to the outcome assessor or analysts, and all outcome data will be labeled using participant ID codes without identifying group allocation. Due to the nature of the behavioral interventions, neither participants nor facilitators will be blinded. We do not expect unblinding to be necessary for the assessor or analysts.

If participants are unable to self-administer via a secure link then measures will be administered verbally by a trained research assistant via telephone or university-managed Zoom and responses input on the behalf of a participant. To support data quality, assessors will be trained in standardized procedures, and data will be entered directly into REDCap, which includes built-in range checks. Duplicate entries and inconsistencies will be identified during routine data cleaning. Each participant will be assigned a unique ID number to ensure confidentiality. All data will be stored on secure University of Manitoba (UM) REDCap servers and transferred to a password-protected UM OneDrive folder in accordance with the data transfer agreement, only the research team will have access to identified data.

To promote retention, participants will receive reminders for each assessment and session, along with technical assistance where needed. In cases where participants discontinue or miss sessions, they will still be invited to complete follow-up assessments, including key outcome measures where possible.

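### The primary superiority comparison is fixed on completers of both stages, a set chosen after randomisation that drops valid week-6 scores because of events in weeks 7–12

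*Protocol article*

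**What the plan says.** All references are to the protocol article.

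- **Framework and allocation** (Patient and public involvement, trial design): "In this RCT the effectiveness and implementation outcomes follow a superiority framework", and "Participants are randomly assigned in a 1:1 ratio to begin either with The CONNECT Program or with the community-based programming".
- **Analysis set** (analysis paragraph under Assignment of interventions): "All analyses will be performed on a per-protocol basis, including only participants who complete both stages". The only relief follows directly: "Sensitivity analyses may include a larger sample, if applicable". No all-randomised analysis is named, either as primary or as secondary.
- **Model and missing data** (same paragraph): linear mixed-effects models adjusting for sequence and baseline; "if data are missing at random, linear mixed models will be used"; multiple imputation or pattern-mixture models are to be considered where key outcomes have much missing data.
- **Follow-up of those who stop** (Assignment of interventions): "In cases where participants discontinue or miss sessions, they will still be invited to complete follow-up assessments, including key outcome measures where possible".
- **Blinding and timing of randomisation** (same section): participants and facilitators are not blinded, and randomisation takes place before enrolment.
- **Assessment schedule** (Table 1): the AAQ-II and all secondary scales are taken at week 0, week 6 and the 6-month follow-up in both sequences, but at week 12 only in the sequence that receives CONNECT second.

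**The concern.** A superiority claim rests on the two randomised groups being comparable apart from the condition received. Finishing 12 weeks of programming is an outcome of participation. The two sequences start with different conditions, and participants know which one they are in, so the reasons for leaving can differ between sequences and can be related to psychological flexibility. A set defined by completion then compares groups that randomisation did not form.

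The assessment schedule makes the rule harder to defend. The usual argument for completers in a crossover trial is that a within-person contrast needs the outcome from both periods. Here the CONNECT-first sequence has no outcome at the end of its control period, so requiring it to finish stage 2 yields no week-12 score. It only removes week-6 scores already recorded. At stake is the validity of the main effectiveness conclusion, and also some precision.

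**Working it through.** **1. Which comparison is affected.** From Table 1, for the AAQ-II:

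| Time | CONNECT-first | CONNECT-second | Contrast available |
|---|---|---|---|
| Week 0 | measured | measured | baseline |
| Week 6 | measured, after CONNECT | measured, after community programming | the two conditions, concurrently |
| Week 12 | not scheduled | measured, after CONNECT | none between sequences |
| Weeks 30–36 | measured | measured | both sequences have by then been offered both conditions |

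Week 6 is the only concurrent post-baseline comparison of the two conditions. A participant with week-0 and week-6 scores who leaves in, say, week 8 contributes fully to that comparison, but the completer rule deletes them.

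**2. The plan's own sample size.** Inputs from the sample-size paragraph (after Table 1): effect 0.5, alpha 0.05, power 80%, target 128. A two-sided two-sample t-test needs 63.8, i.e. 64 per group, 128 in total, with power 80.1%. The figure is reproduced and contains no allowance for dropout. The article attaches the 64 to delivery mode; with 1:1 allocation, 128 also gives 64 per sequence.

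**3. Size of a possible selection bias.** Let p be the proportion excluded from a sequence and g the amount, in SD, by which excluded participants do worse than completers (negative if they do better). The completer mean exceeds the full-sequence mean by p × g, so

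bias in favour of CONNECT at week 6 = p₁g₁ − p₂g₂ (1 = CONNECT-first, 2 = CONNECT-second).

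The article gives neither p nor g. All values below are assumptions.

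| p₁, g₁ | p₂, g₂ | Bias (SD) |
|---|---|---|
| 0.20, 0.3 | none | +0.06 |
| 0.20, 0.5 | none | 0.20 × 0.5 = +0.10 |
| 0.30, 0.5 | none | +0.15 |
| 0.20, 0.5 | 0.10, 0.5 | 0.10 − 0.05 = +0.05 |
| 0.20, 0.5 | 0.20, 0.5 | 0.10 − 0.10 = 0 |
| 0.10, 0.5 | 0.20, 0.5 | 0.05 − 0.10 = −0.05 |

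The shift of 0.10 SD is 0.10 / 0.5 = one fifth of the planned effect. The last rows show that the sign depends on which sequence is more selected.

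**4. Precision.** With 20% excluded, 64 × 0.80 = 51.2 per sequence remain. The planned model adjusts for baseline. If r is the correlation between baseline and week-6 scores (not stated, so a range is shown), the effect in residual SD units is 0.5 / √(1 − r²). Two-sample t-test power, two-sided 0.05:

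| r | Effect | 64 per sequence | 51.2 per sequence |
|---|---|---|---|
| 0 | 0.500 | 80% | 71% |
| 0.3 | 0.524 | 84% | 75% |
| 0.5 | 0.577 | 90% | 82% |
| 0.7 | 0.700 | 98% | 94% |

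At 20% exclusion the loss is about 4 to 9 percentage points. Only part of it is avoidable, because non-completers are to be assessed where possible and some will have no score.

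**The case against.** Nothing elsewhere in the article commits to an all-randomised primary analysis, and the completer rule is an explicit statement rather than a detail left to an analysis plan. The strongest objections concern what else a reader might infer.

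- **That the rule inflates the benefit.** This would follow if people mainly left CONNECT because it did not suit them. But the rule also removes CONNECT-first participants who improve and then skip the usual programming, and worse-off CONNECT-second participants who leave before CONNECT starts. Both move the estimate the other way. The document does not fix the sign.
- **That outcome data from people who stop are thrown away.** They are left out of the main analysis, but they could enter the optional larger-sample analysis. Someone who misses sessions may also still count as a completer, since completion is not defined.
- **That the missing-data methods have nothing left to do.** Completers can still miss single assessments or the 6-month follow-up.
- **That completing the control stage cannot be verified.** Table 1 says of the weekly check-in "Weekly administration during the CONNECT Program sessions only; not completed during control condition". This shows only that one instrument is not scheduled in control. The text after Fig 1 and the Monitoring section mention attendance tracking and oversight in general terms, so the absence of any control record does not follow.
- **That power falls from 80% to 71%.** That is an unadjusted test at an assumed 20% exclusion; the plan adjusts for baseline.

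These objections limit the size and direction of the problem. They do not justify selecting the primary analysis set on a post-randomisation event, and an optional sensitivity analysis leaves the primary result unchanged.

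**Conclusion.** The concern holds: the completers-only set is the wrong primary population for this superiority comparison. It can bias the effect in either direction, and it removes usable week-6 scores because of later events without gaining a week-12 score in the CONNECT-first sequence. It also leaves out of the main analysis outcomes that the trial intends to seek from people who stop, which the planned mixed model could use.

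The size cannot be set from the document because no dropout rate is given. The 0.10 SD illustration rests on 20% exclusion in one sequence, a 0.5 SD gap and no selection in the other. The loss of precision depends on dropout, on the baseline correlation and on how many non-completers are assessed.

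This should be corrected before the data are analysed, because it governs the main conclusion.

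**What to change.** Replace the per-protocol sentence with:

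> The primary analysis includes all randomised participants who consented and have at least one AAQ-II score, analysed in the sequence to which they were randomised, using every available AAQ-II score in the planned likelihood-based mixed model, valid under missing at random; the number randomised without any score is reported by sequence. An analysis of participants who complete both stages is a sensitivity analysis.

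The conditions on consent and on having a score are needed because randomisation precedes enrolment, so some randomised people may never provide data. Use the multiple-imputation or pattern-mixture models already listed as sensitivity analyses for departures from missing at random.

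**Cost.** One paragraph is amended and no new data are needed. The article describes recruitment as ongoing, with endpoint collection expected by 30 September 2026, so the change can be made prospectively. The estimate may differ from the completers-only estimate and may be smaller. Participants without follow-up scores add little information, so the lost precision is recovered only in part.
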